**Clinical data:**

General background data from the chart and supplementary data from the history form, see appendix 1 a+b. Data on pregnancy complications, birth, etc., from the chart, midwife notes and the obstetrical database. Maternal weight from pregnancy chart is noted as the weight at the end of pregnancy.

**Data on follow-up:**

If the patient has given permission for follow up, they are contacted by letter 8 weeks after birth and again in connection to summons to follow-up OGTT 1 year after birth and given a short questionnaire regarding the height and weight of the child and information on breast feeding. (Appendix 7)

**Primary endpoints:**

Maternal weight increase

Birth weight – in relation to GA

Method of birth: uncomplicated vaginal birth / instrumental delivery / sectio

**Secondary endpoints:**

2 hour blood glucose with OGTT

Lipid profile

Presence of hypertension or preeclampsia

Induction

Need to promote uterine contractions

Hypoglycaemia in child

Placenta’s weight

Breast feeding

**B.** **Questionnaire study: Elucidation of dietary habits/ diet changes in obese pregnant women med BMI≥30 kg/m², with high or low weight grain during pregnancy.**

**Hypothesis:**

Ingestion of “Mediterranean diet”

- Reduces weight increased during pregnancy.
- Lessens risk of pathologic glucose intolerance in pregnancy and thereby risk of GDM.
- Reduces risk of macrosomia (FV>4000g)
- Reduces risk of pre-term birth.

**Method:**

A detailed dietary history (360 questions) will be taken at the beginning and end of pregnancy using a questionnaire used and validated in the study “Better health for mother and child”(The Danish National Birth cohort). Importance of changes in the individual elements of the diet for the increase in maternal weight, fetal weight, length of pregnancy and pregnancy complications will be analysed.

Collection and analysis of date will be done in association with statisticians at Statens

Seruminstitut (the State Serum Institute).

**Calculation of strength in part-project B:** With an expected middle value for cholesterol of 270 mg/dl in week 37, with a standard deviation of 40 mg/dl (25), 129 women are needed in each group to detect a 5% reduction in cholesterol (alfa = 0.05: beta = 0.20). This number with a strength of 65% and an alfa of 0.05 will determine a 50% increase in pregnancy complications (prerequisite 25% pregnancy complications.) We aim to include 140 in each group in order to allow for any dropouts, **thus a total of 420 women**.

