**PURPOSE:**

- To analyse the importance of changes in elements of the diet for maternal weight gain, length of pregnancy and complications of pregnancy.

**MATERIALS AND METHODS**.

1. **Randomised intervention study. Effect of physical activity measure with use of a pedometer together with dietary intervention in heavily obese pregnant women.**

Hypothesis:

Physical activity and or intensive dietary intervention will lessen material weigh gain during pregnancy in obese pregnant women and lessen the risk of

1. pathologic glucose tolerance during pregnancy and thereby the risk of GDM.

2. macrosomia.

3. reduce risk of caesarean section because of dystocia.

**Inclusion criteria:** BMI ≥30 kg/m².

Normal pregnancy with normal neck fold scan. Informed consent.

**Exclusion criteria:** Under 18 years. Non-Danish speaker. Serious disease in mother or fetus. Alcohol or drug dependency.

**Inclusion period**: 18 months during which 600 children are born at Hvidovre Hospital of mothers with a pre-pregnancy BMI ≥ 30 kg/m². With an expected participation percentage of 70, we expect to include 420 in the study.

In accordance with the standard regimen, all obese pregnancy women with BMI≥30 are offered:

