**Method:**

After the first visit to the dietician during which a detailed dietary history is taken, all included obese pregnant women will be telephone randomised 1:1:1, to intervention groups 1, 2 or to general standard regimen for all obese pregnant women as given above.

**Intervention aim:** Weight gain: <5 kg

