1. Pregnant women who come to consultation with the dietician, but who **do not** want to take part in the project:

- After consultation with dietician the project leader requests that the history form is filled out and goes through it.
- The pregnant woman follows the usual pregnancy programme and standard regimen.

1. Pregnant women who do not respond to summons to the dietician and who have not received oral information about the project:

- The pregnant woman comes to a consultation with a doctor in accordance with the standard regimen in order to arrange a malformation scan at GA 18-22. The history form is asked about. If this has not been filled out, it is given out again and the pregnant woman is asked to fill it out.

**Project blood tests:** In all three groups an oral glucose tolerance test (OGTT) is done as part of the standard regimen at 13–20 and 27–30 weeks. In connection with these tests, blood will be taken for determination of c-peptid, CRP and lipid profile, (triglycerides, HDL, LDL, and total cholesterol) A research biobank will be set up (20 ml blood per blood sampling session) with the aim of later determination of, among others, IL-18, IL-6, TNF alfa.

Blood tests will be stored for 10 years

The material will only be used for analyses regarding determination of conditions related to pregnancy, physical activity, diet and obesity.

Plasma glucose and OGTT measured regularly at the department of biochemistry using routine methods.

For the OGTT the patient is fasting and ingests 75 g glucose. Plasma glucose determined initially and after 2 hours.

Extra tubes for measurement of markers for glucose metabolism are centrifuged, pipetted off and stored at –80 degrees until later analysis.

**Cord Blood samples** are taken immediately after birth and cutting of umbilical cord. If possible up to 20 ml blood is taken, and stored in the research biobank.

**Ultrasound (US) scans at GA 37-38:** Estimation of weight and measurement of amniotic fluid. This is done by project leader in patient groups 1, 2 and 3. In connection with this, the dietary history form is filled out again (see below) and the patient weighed.

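### Part B's change-in-diet analysis uses a form taken at GA 37-38, so it cannot inform on pre-term birth and is open to reverse causation for GDM; inclusion diet should be used for these outcomes

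*Protocol*

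**What the plan says.** All references are to the protocol.

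- **Purpose of the questionnaire study:** "To analyse the importance of changes in elements of the diet for maternal weight gain, length of pregnancy and complications of pregnancy".
- **Part B, Method:** the analysis planned is of "Importance of changes in the individual elements of the diet for the increase in maternal weight, fetal weight, length of pregnancy and pregnancy complications". The data source is described as "A detailed dietary history (360 questions) will be taken at the beginning and end of pregnancy".
- **Part B, Hypothesis:** the exposure is worded differently, as "Ingestion of “Mediterranean diet", with no mention of change. Two of the four listed effects are "Reduces risk of pre-term birth" and "Lessens risk of pathologic glucose intolerance in pregnancy and thereby risk of GDM".
- **Timing of the first form:** the Method of the randomised study states "After the first visit to the dietician during which a detailed dietary history is taken, all included obese pregnant women will be telephone randomised 1:1:1". The design overview table places this form at inclusion, ahead of the first OGTT.
- **Timing of the second form:** the paragraph on ultrasound scans at GA 37-38 says that at this visit "the dietary history form is filled out again (see below) and the patient weighed". The overview table agrees.
- **Timing of GDM screening:** the standard regimen places the OGTTs at weeks 13-20 and 27-30.

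The protocol describes no diet form between these two, none at an early delivery, and no rule for women who give birth before the GA 37-38 visit.

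**The concern.** A change score exists only for women who complete both forms. The second form is scheduled after every pre-term birth has happened and after both GDM screens have been read. The exposure in the stated analysis is therefore missing for every woman with one of the outcomes, and for another it is partly measured after the outcome.

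If the Method is followed as written, the analysis gives no estimate for pre-term birth. For pregnancy length it gives an estimate restricted to pregnancies that reached term. For GDM it gives an association whose direction in time is unclear, and which a reader could take as support for, or against, the hypothesis that the diet lowers the risk.

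**Working it through.** The protocol states no figure to reproduce here. The check compares the week of each diet form with the week of each outcome.

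**Order of events as scheduled**

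| Step | Time | Source |
| --- | --- | --- |
| First diet form | Inclusion, before randomisation | Method; overview table |
| First OGTT | Weeks 13-20 | Standard regimen; overview table |
| Second OGTT | Weeks 27-30 | Standard regimen; overview table |
| Pre-term births | Before week 37 (assumed definition) | Not defined in the protocol |
| Second diet form | GA 37-38 | Ultrasound paragraph; overview table |

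**Pre-term birth.** Let D1 be diet on the first form and D2 diet on the second; the exposure is D2 − D1. D2 exists only if the woman is still pregnant at GA 37-38. A woman who delivers before week 37 has no D2, so:

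- pre-term births among women with a change score = 0, whatever the pre-term rate or sample size;
- the outcome does not vary in the analysable set, so no association can be estimated.

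The protocol gives no pre-term rate. Over an assumed range, with the planned total of 420:

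- at 4%: 0.04 × 420 = 16.8, about 17 women;
- at 12%: 0.12 × 420 = 50.4, about 50 women.

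None of these women has a change score. Imputing one would rest entirely on women who delivered at term.

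**Length of pregnancy.** The same condition truncates this outcome from below at about 37 weeks. Any relation between diet and early delivery is removed by the selection.

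**GDM.** Interval from OGTT to second form:

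- first OGTT: shortest 37 − 20 = 17 weeks, longest 38 − 13 = 25 weeks;
- second OGTT: shortest 37 − 30 = 7 weeks, longest 38 − 27 = 11 weeks;
- overall: 7 to 25 weeks.

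Suppose diet has no effect on GDM, but a diagnosis shifts later diet (or its reporting) by δ. The expected change is then m among women without GDM and m + δ among women with GDM who reach the visit. The analysis would show a difference of (m + δ) − m = δ, produced wholly by the diagnosis. If δ is a move towards the recommended diet, this works against finding a protective association. The protocol gives nothing from which to size δ.

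**Inclusion diet.** D1 is scheduled before both OGTTs and before any pre-term birth, and is planned for every included woman. Relating D1 to these outcomes keeps all events and the correct order in time.

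**The case against.** A reader might infer that the pre-term and GDM hypotheses cannot be tested at all. The protocol does not support that. The Hypothesis section speaks of ingesting the diet, not of changing it, and the inclusion form can be related to both outcomes with all events. What remains is that the stated Purpose and Method name only changes in diet. The GDM change analysis can also be run; it is biased, not impossible.

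A reader might also infer that the GDM association would reverse sign. The protocol does not describe dietary management after a GDM diagnosis, and all women receive Mediterranean-type advice at the first dietician visit whatever the OGTT shows. That diet changes after a diagnosis is a reasonable inference, but its size is unknown. D1 is also measured before diagnosis, so only one component of the change score is affected.

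Three further points carry weight:

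- Part B is sized by group (140 each, 420 in total, matching the three randomised arms), and both outcomes could be compared between arms without a second form. That is true, but such a comparison addresses allocation to the intervention, whereas Part B's stated purpose is the role of changes in diet.
- Neither pre-term birth nor a GDM diagnosis is a listed primary or secondary endpoint, so the randomised inference is untouched. This lowers the severity.
- The choice of form for each outcome could be settled in an analysis plan. That holds for using inclusion diet. No later plan can recover a form that was never scheduled, and the protocol's own text points to change.

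Finally, moving the second form to weeks 27-30 may look like a full cure. It is not: it would still follow any GDM found at weeks 13-20 and any delivery before that visit.

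**Conclusion.** The point holds for the change-in-diet analysis, not for the hypotheses as worded. That analysis has zero pre-term events by construction, covers pregnancy length only from about 37 weeks, and cannot be read causally for GDM because both screens precede the second form by 7 to 25 weeks.

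The zero rests on taking pre-term birth as delivery before 37 weeks and on the second form being completed at GA 37-38 as scheduled. The range of 17 to 50 affected women rests on assumed rates of 4% to 12%. The usefulness of inclusion diet rests on the first form being completed before the first OGTT, as the overview table orders it.

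The macrosomia and weight-gain hypotheses are less affected, although their change analyses also cover only women who reach the GA 37-38 visit. This is a limited correction to an observational sub-study and does not threaten the randomised comparison.

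**What to change.** In the Method of Part B:

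- relate pre-term birth, length of pregnancy and GDM to diet at inclusion;
- limit the analysis of change from inclusion to GA 37-38 to outcomes that follow the second form, such as birth weight at term, and state that it applies only to women who reach that visit;
- align the Purpose of the questionnaire study, which currently names change in diet for pregnancy length and complications.

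This needs no new data. Its downside is that inclusion diet does not show the effect of changing diet on these outcomes.

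If that question matters, the same form could also be completed at the existing week 27-30 OGTT visit, before the result is known. The change from inclusion to that visit should then be used only for:

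- pre-term birth and pregnancy length, among women still pregnant at that visit;
- GDM first found at weeks 27-30, among women with a normal OGTT at weeks 13-20.

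The cost is one extra 360-question form per woman and someone to administer it at a visit for which the protocol describes no project-leader contact. The change in diet is also seen over a shorter interval.

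### The only sample-size calculation rests on week-37 cholesterol, which the schedule does not collect; it gives no power for any primary endpoint, and its figures do not follow from its own inputs

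*Protocol*

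**What the plan says.** The calculation stands at the end of the Method section of project B, the questionnaire study. It takes as planning values "With an expected middle value for cholesterol of 270 mg/dl in week 37, with a standard deviation of 40 mg/dl" and concludes that "129 women are needed in each group to detect a 5% reduction in cholesterol" ("alfa = 0.05: beta = 0.20"). It does not say whether alpha is one- or two-sided. A second statement follows: "This number with a strength of 65% and an alfa of 0.05 will determine a 50% increase in pregnancy complications", with the base rate given as "prerequisite 25% pregnancy complications". The size is then raised to 140 per group for dropouts, 420 in total.

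The same 420 appears under Inclusion period for the randomised study (70% of 600), and the Method section of that study randomises 1:1:1 to three groups.

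Under Project blood tests, lipid sampling is tied to the glucose tolerance tests at weeks 13-20 and 27-30: "In connection with these tests, blood will be taken for determination of c-peptid, CRP and lipid profile". The design overview repeats the project tests at one year post partum. Its row for weeks 37-38 has a dietary history and an ultrasound and an empty blood-test cell. The text on the week 37-38 scan adds a weighing but no blood sample.

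The Primary endpoints section lists "Maternal weight increase", birth weight in relation to gestational age, and method of birth. "Lipid profile" is listed under Secondary endpoints.

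**The concern.** A sample-size statement should tell the reader what difference in the main outcome the trial can detect. This one has three faults.

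- **Wrong time.** Its 80% power refers to cholesterol at a week when the trial draws no blood.
- **Wrong outcome.** It gives no SD, target difference or power for any primary endpoint. A neutral result on weight gain, birth weight or method of birth could not be read against a planned detectable effect.
- **Wrong arithmetic.** The 129 and the 65% are both more favourable than the stated inputs allow under a two-sided test.

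The heading adds to the confusion. A reader looking for the basis of the randomised trial's size will not find it under the randomised trial.

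**Working it through.** **1. Which study the calculation sizes.** 3 x 140 = 420, and 600 x 0.70 = 420. Three equal groups match the 1:1:1 allocation. Whatever its heading, this is the size of the randomised trial.

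**2. Is the sizing variable collected?**

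| Time | Maternal lipids scheduled? |
| --- | --- |
| Weeks 13-20 | Yes |
| Weeks 27-30 | Yes |
| Weeks 37-38 | No (diet form, ultrasound, weighing) |
| Birth | No (cord blood only) |
| One year post partum | Yes (project tests) |

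The table and the text of the protocol agree with each other and disagree with the calculation.

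**3. The 129 per group.** Inputs from the protocol: mean 270, SD 40, 5% reduction, alpha 0.05, power 80%. The difference is 0.05 x 270 = 13.5 mg/dl. Formula: n = 2(z_alpha + z_power)² SD² / difference².

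- Two-sided: 2 x (1.960 + 0.842)² x 1600 / 182.25 = 2 x 7.849 x 1600 / 182.25 = 137.8, so **138** (139 by the t-test).
- One-sided: 109.
- Difference rounded up to 14 mg/dl, two-sided: 2 x 7.849 x 1600 / 196 = 128.1, so 129.

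Of these variants, only the rounded difference (5.2% of 270) gives 129. For the stated 13.5 mg/dl at 129 per group, z = 13.5 / (40 x √(2/129)) − 1.960 = 2.71 − 1.96 = 0.75, a power of **77.4%** (77.0% by the t-test). At 140 it is 80.6% (80.3%).

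Dropout room: the protocol implies 1 − 129/140 = 7.9%. With 138 needed it is 1 − 138/140 = 1.4%; with 139 it is 0.7%.

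**4. The 65% for complications.** Base 25%; a 50% relative increase gives 37.5%; n = 129. The pooled proportion is 0.3125.

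z = [0.125 x √129 − 1.960 x √(2 x 0.3125 x 0.6875)] / √(0.25 x 0.75 + 0.375 x 0.625) = (1.420 − 1.285) / 0.650 = 0.208, a power of **58.2%**.

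| Test at n = 129, 25% vs 37.5% | Power |
| --- | --- |
| Two-sided | 58.2% |
| Two-sided, continuity-corrected | 52.9% |
| One-sided | 70.1% |
| One-sided, continuity-corrected | 65.2% |

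The stated 65% thus matches a one-sided, continuity-corrected test, while 129 for cholesterol needs a two-sided test and a rounded difference. The two figures do not share one convention. A halving from 25% to 12.5%, which is the hypothesised direction, would have 73.2% power two-sided.

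**5. What the planned size detects on the primary endpoints.** The protocol gives no SD for any of them, so the result is in SD units: (1.960 + 0.842) x √(2/n), for one pairwise comparison at two-sided 0.05 and 80% power.

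- n = 129: 0.349 SD (0.350 by the t-test).
- n = 140: 0.335 SD (0.336 by the t-test).
- n = 129 with alpha split over three primary endpoints (0.05/3, illustration only): (2.394 + 0.842) x √(2/129) = 0.403 SD.

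If the SD of weight gain is assumed to be 5 to 10 kg, 0.349 SD is 1.7 to 3.5 kg at n = 129. If caesarean section is taken as a yes/no outcome with an assumed control rate of 25% or 30%, the detectable fall at n = 129 is to about 11.6% or 15.4% (12.0% or 16.0% at n = 140), roughly a halving.

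**The case against.** The strongest defence is that cholesterol is not foreign to the trial. Total cholesterol is measured at two points in pregnancy and again at one year. Lipid profile is a stated purpose and a listed secondary endpoint. The week-37 mean and SD can be seen as planning values taken from a cited source, since the protocol nowhere plans a week-37 cholesterol analysis. There is also a second power statement, for complications, which relates loosely to listed outcomes such as hypertension or preeclampsia. The project B heading may be a labelling slip in a translated text.

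Much of this stands, and it limits the point. A reader might infer that the trial never measures cholesterol, or that no stated power bears on anything it will report. The documents support neither: only the week-37 value is missing, and both power statements touch secondary outcomes. A reader might also infer that the week-37 mean and SD are wrong for weeks 27-30. That is not shown either way, because the protocol gives no values for those weeks.

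The defence does not reach the primary endpoints. Nor does the complications statement fill the gap: the composite is undefined, the power is low, and an increase is powered while the hypotheses are reductions. Reading it as a fall from 37.5% to 25% gives the same 58.2%.

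It is also fair to object that a detectable difference worked back from a fixed size describes that size and does not justify it. That is true. The restated figures would let readers judge the size; they would not prove it adequate.

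**Conclusion.** The point holds in this form. The only sample-size calculation is filed under the wrong project, is anchored to a time with no blood sample, and states no power for any of the three primary endpoints. Its figures are also too favourable. The stated inputs need 138-139 per group, not 129; power at 129 is about 77%, not 80%; and the allowance for dropout falls from 7.9% to about 1%. The complications power is about 58% two-sided, not 65%.

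These recalculations assume a two-sided 0.05 test and one pairwise comparison, because the protocol does not state sidedness. The detectable 0.35 SD needs no outside figure. The kg values and caesarean rates rest on the assumed ranges shown. All are optimistic if alpha is to be shared across endpoints or arms. The documents do not show that 420 women are too few for the primary endpoints; they show that the question was not addressed.

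**What to change.** Change the protocol text, with no change in enrolment or blood sampling:

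1. Place the calculation under project A, the randomised trial.
2. State what the planned size detects for maternal weight increase: about 0.35 SD with 129 evaluable per group, or 0.34 SD with 140, at 80% power for one pairwise comparison at two-sided 0.05. Give the assumed SD in kg and its source. If alpha is to be split over the three primary endpoints, show that figure too (about 0.40 SD at 129).
3. Add detectable differences for birth weight and method of birth as supporting figures, with their assumptions.
4. Tie the lipid figure to the week 27-30 sample, with a mean and SD for that time, and label it secondary.
5. State sidedness. Correct 129 with 80% power to 138-139 per group (or to about 77% at 129), and 65% to about 58%. State the complications effect in the direction of the hypotheses and define the composite.

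The cost is some redrafting and a source for the SD of weight gain. The downside is that the stated figures become less favourable.

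### The protocol's own inputs require 138–139 women per group (two-sided), not 129, for 80% power on a 5% cholesterol reduction. This leaves a dropout margin of 1–2 per group, and the 65% complications figure rests on a different convention.

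*Protocol*

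**What the plan says.** The calculation stands in the Protocol, section B (Questionnaire study), under Method, in the paragraph on strength in part-project B. It starts "With an expected middle value for cholesterol of 270 mg/dl in week 37", gives an SD of 40 mg/dl, and concludes that "129 women are needed in each group to detect a 5% reduction in cholesterol (alfa = 0.05: beta = 0.20".

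It then carries the same group size over to a second outcome: "This number with a strength of 65% and an alfa of 0.05 will determine a 50% increase in pregnancy complications", taking 25% as the underlying complication rate. Finally it rounds up: "We aim to include 140 in each group in order to allow for any dropouts", for a total of 420.

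The paragraph does not say whether the tests are one- or two-sided, which test is meant for complications, or what dropout rate is expected. Allocation is 1:1:1 (section 1, Method), so a pairwise comparison has equal groups.

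**The concern.** All the numerical inputs for the cholesterol calculation are given except sidedness, so the result can be checked, and neither choice of sidedness returns 129. This paragraph is the only power calculation in the protocol. A reader learns from it that 129 evaluable women per group give 80% power for a 5% reduction, that 11 per group are spare, and that the same 129 give 65% power for complications. If the first figure is too low, part of the supposed dropout allowance is needed simply to reach 80%. If the two power figures use different conventions, the single alpha of 0.05 attached to both does not mean the same thing each time.

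**Working it through.** **Inputs, all from the power paragraph:** mean 270 mg/dl; SD 40 mg/dl; reduction 5%, so 0.05 × 270 = 13.5 mg/dl; alpha 0.05; power 0.80; complication rate 25%, and 1.5 × 25% = 37.5%; 129 per group, raised to 140. **Assumption:** sidedness is not stated, so both versions were run.

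**1. Group size for cholesterol.** n = 2(z_alpha + z_power)²(SD/difference)².

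- Two-sided: 2 × (1.960 + 0.842)² × (40/13.5)² = 137.8, so 138. The t-test gives 138.8, so 139.
- One-sided: 2 × (1.645 + 0.842)² × (40/13.5)² = 108.6, so 109.
- Two-sided with 14 mg/dl: 2 × (1.960 + 0.842)² × (40/14)² = 128.1, so 129. This reproduces the stated figure, but 14/270 = 5.2%.

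Rounded values of 7.0 and 1.0 mmol/l also give 129 (difference/SD = 0.35). Those units are an assumption, since the protocol works in mg/dl.

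**2. Power for 13.5 mg/dl, two-sided.** Power = Φ(difference / (SD√(2/n)) − 1.960).

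- n = 129: 13.5 / (40 × 0.1245) = 2.711, and Φ(0.751) = 77.4% (t-test 77.0%).
- n = 140: 13.5 / (40 × 0.1195) = 2.824, and Φ(0.864) = 80.6% (t-test 80.3%).
- One-sided at n = 129: 85.7%, so this does not return 80% either.

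**3. Dropout margin.**

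- As stated: 140 − 129 = 11 per group (7.9% of 140).
- Two-sided from the stated inputs: 140 − 138 = 2 per group (1.4%), or 140 − 139 = 1 by t-test.

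**4. Complications, 25% against 37.5%, n = 129.** With mean rate 0.3125, √(2 × 0.3125 × 0.6875) = 0.6555 and √(0.25 × 0.75 + 0.375 × 0.625) = 0.6495. Power = Φ((0.125√n − z_alpha × 0.6555)/0.6495); the continuity correction replaces 0.125 by 0.125 − 1/n.

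| Test | Two-sided | One-sided |
| --- | --- | --- |
| Pooled variance | 58.2% | 70.1% |
| Unpooled | 58.9% | 70.6% |
| Arcsine | 58.5% | 70.2% |
| Continuity-corrected | 52.9% | 65.2% |

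Exact calculations, two-sided, give 58.8% (chi-square) and 53.5% (Fisher). The stated 65% appears only in the one-sided, continuity-corrected cell. Two-sided with pooled variance, 65% power would need 151 per group, and 140 per group with no loss gives 61.8%.

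**5. Is there a common basis?** Two-sided, complications power at 129 is at most about 59%. One-sided, cholesterol needs 109. Comparing both intervention arms together with control (258 against 129) does not help: two-sided power is 87.9% for cholesterol and 69.9% for complications; one-sided it is 93.1% and 80.3%. No convention tried gives 129 and 65% together.

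**The case against.** The strongest reply is that the cholesterol gap is rounding. A difference of 14 instead of 13.5 mg/dl explains it entirely, the inputs are round planning values, and under 3 power points are at stake on an outcome (lipid profile) that the protocol lists as secondary. That stands and limits the severity, but it does not make 129 follow from a 5% reduction.

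Four stronger readings are tempting, and the document does not support them.

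- **That 65% is simply wrong.** Sidedness and test are not stated, and a one-sided, continuity-corrected test gives 65.2% at exactly 129. What can be said is that this basis does not fit the one that yields 129.
- **That there is no dropout allowance, or that any loss takes power below 80%.** Of 140 women per group, one can be lost and power stays at 80% by the t-test (80.1% at 139). Two can be lost under the normal approximation (80.05% at 138). Nor is 7.9% a planned dropout rate; it only follows from 129 and 140.
- **That an increase in complications contradicts the hypotheses.** Those are worded as reductions, for example "reduce risk of caesarean section because of dystocia". But 25% against 37.5% can be read with the higher rate under standard care, and two-sided power is the same either way. The paragraph should say which arm is meant; the arithmetic is unaffected.
- **That 420 is therefore the wrong size.** The protocol also reaches 420 from expected recruitment (600 births × 70%), and 140 per group gives 80% power for 13.5 mg/dl if almost nobody is lost.

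**Conclusion.** The point holds, at minor to moderate severity. From the stated inputs, 129 per group does not give 80% power for a 5% cholesterol reduction. Two-sided, 138–139 are needed and power at 129 is 77%. The dropout margin within 140 shrinks from 11 to about 1–2 women per group. The complications power is 58% on the same two-sided basis (53% with continuity correction), and 65% belongs to a different convention.

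The margin and the 58% assume two-sided tests, an inference from the fact that 129 matches a two-sided calculation at 14 mg/dl. If the sponsor meant one-sided tests throughout, the margin would be ample (140 − 109 = 31 per group), but 129 would still not follow from the inputs. Under either reading the paragraph needs correcting; the design does not.

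**What to change.** Keep 420 and rewrite the one paragraph on a single two-sided 0.05 basis, naming the test for each outcome:

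- **Cholesterol:** 138 per group (139 by t-test) for 80% power at 13.5 mg/dl (5%). Alternatively, keep 129 and give the difference as 14 mg/dl (5.2%).
- **Power for 13.5 mg/dl:** 77% with 129 evaluable per group, 80% with 140.
- **Dropout:** if 80% power for 5% is claimed, state the margin as 1–2 women per group. The 11-woman margin fits only the 14 mg/dl version.
- **Complications:** 58% power at 129 per group for 25% against 37.5%, saying which arm is assumed to have the higher rate.

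The cost is the rewording and a slightly less favourable power statement. Recruitment and design are unchanged.

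### The protocol's own inputs require 138–139 women per group, not 129, so a target of 140 leaves almost no reserve for dropout at 80% power

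*Protocol*

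**What the plan says.** The only sample-size calculation in the Protocol is in part B (the questionnaire study), at the end of its Method section. Its inputs are an "expected middle value for cholesterol of 270 mg/dl in week 37" and an SD of 40 mg/dl. The conclusion is that "129 women are needed in each group to detect a 5% reduction in cholesterol (alfa = 0.05: beta = 0.20". The paragraph continues: "We aim to include 140 in each group in order to allow for any dropouts", and arrives at 420 women in total.

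The Method section of the randomised study has women "telephone randomised 1:1:1, to intervention groups 1, 2 or to general standard regimen", so each pairwise comparison is between groups of equal size. The paragraph does not state whether the test is one- or two-sided, which test is used, the scale of analysis, or a dropout rate.

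**The concern.** Every input to the usual two-means formula is given except sidedness, so the result can be checked, and under the conventional two-sided reading it comes out too low. The calculation matters because the paragraph derives the 3 × 140 = 420 women from 129 plus a margin. If 129 is too small, the margin that appears to cover dropout is mostly needed to reach 80% power in the first place. A reader would take the plan to have 80% power after losing up to 11 women per group, which it does not have.

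**Working it through.** **Inputs** (Protocol, part B, strength calculation; allocation from the Method section of the randomised study)

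- Mean 270 mg/dl; SD σ = 40 mg/dl
- Effect: δ = 0.05 × 270 = 13.5 mg/dl, standardised 13.5/40 = 0.3375
- α = 0.05, taken as two-sided (assumption); β = 0.20, so z-values 1.960 and 0.842
- Equal group sizes

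**Attempt to reproduce 129**

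n per group = 2(z₁₋α/₂ + z₁₋β)² σ² / δ²

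- With δ = 13.5: 2 × 7.849 × 1600 / 182.25 = 137.8, so **138**. The t test (noncentral t) gives 138.8, so **139**.
- The stated 129 is 9 to 10 women per group short, about 7%. The choice between z and t moves the answer by only one.

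**Other readings tried**

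| Reading | n per group |
|---|---|
| One-sided, δ = 13.5 | 108.6, so 109 |
| Two-sided, Bonferroni for 2 comparisons | 167 |
| Two-sided, Bonferroni for 3 comparisons | 184 |
| Log scale, CV = 40/270 | 130 |
| Three-group F test, one group differing by 13.5 | 128 |
| Two-sided, δ rounded up to 14 | 2 × 7.849 × 1600 / 196 = 128.1, so 129 |

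Only the last gives 129 exactly (normal approximation; the t test gives 129.1). But 14/270 = 5.2%, which is not the stated 5%. That rounding is the source of 129 is an inference; the mismatch does not depend on it.

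**Power for 13.5 mg/dl, two-sided t test**

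| Evaluable per group | Loss from 140 | Power |
|---|---|---|
| 140 | 0% | 80.3% |
| 139 | 0.7% | 80.1% |
| 135 | 3.6% | 78.9% |
| 129 | 7.9% | 77.0% |
| 126 | 10% | 76.1% |

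The normal approximation gives 77.4% at 129 and 80.6% at 140. At 129 per group, the difference detectable with 80% power is 14.0 mg/dl.

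**Dropout reserve**

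- As the plan implies: 140 − 129 = 11, and 11/140 = 7.9%
- Against 138: 140 − 138 = 2, and 2/140 = 1.4%
- Against 139: 140 − 139 = 1, and 1/140 = 0.7%

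**The case against.** Five points can be made for the plan.

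1. **The reading is assumed.** Sidedness, test and scale are not stated, and two other analyses come close to 129: log scale (130) and a three-group F test (128). This is a reason to state the two-sided, raw-scale assumption openly. It does not rescue the figure: the Protocol gives a mean and SD in mg/dl and a reduction to detect, describes neither alternative, and neither returns 129.
2. **The effect is small.** This stands. Power falls gradually, by 3 points at 129, and full retention of 140 still gives 80.3%. The reserve of 11 is also a subtraction, not a stated rate.
3. **420 has a second basis.** This stands too. Under the inclusion period, 600 births × 70% participation = 420, so the enrolment target would survive. The strength paragraph nevertheless presents 420 as the result of its own calculation.
4. **Cholesterol is a marginal variable.** Lipid profile is a secondary endpoint, and the design overview shows no blood test at weeks 37–38. That limits how much this power figure tells us about the trial, and correcting the arithmetic does not change that. It does not make the stated number right.
5. **The next sentence depends on 129.** It claims 65% power for a 50% increase in complications from 25%. For 25% versus 37.5%, two-sided without continuity correction, power is 58% at 129 and 61% at 138. So that sentence needs rechecking in the same edit.

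**Conclusion.** The concern holds. For a two-sided comparison of two raw means at the stated inputs, 80% power needs 138 women per group (139 by t test), and 129 gives about 77%. A one-sided test does not explain the figure. The enrolment of 140 per group is just enough with essentially complete follow-up, so the plan can claim 80% power or a meaningful dropout allowance for a 5% reduction, but not both. The size is modest: about 3 points of power at 129 and 4 at 10% loss. It is an error in what the plan states about its power, and it does not by itself require a larger trial.

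**What to change.** Keep 420 and restate the calculation, for example: *For a two-sided t test at α = 0.05, 139 women per group (138 by normal approximation) are needed to detect a 5% (13.5 mg/dl) reduction with 80% power. With 140 per group and no dropout, power is 80%. With 8% dropout (129 evaluable) power is 77% for 13.5 mg/dl, or 80% for a difference of 14 mg/dl (5.2%).*

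Remove the claim that 140 allows for dropouts at 80% power. If another test or scale was intended, name it and give the calculation that leads to 129. In the same edit, recheck the 65% power claim for complications and tie it to an explicit group size, because it currently refers back to 129.

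The cost is a corrected paragraph and a slightly less favourable power statement. No additional patients are needed and the design does not change.
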